### Primary intervention effectiveness outcome

#### World Health Organization Disability Assessment Schedule Child Version (WHODAS- Child 2.0)

The WHODAS is a 36-item questionnaire measuring functioning and disability. The items represent cognition, mobility, self-care, getting along with others, life activities, and participation in the society. The interviewer administered proxy version (caregiver report) will be used as it is expected children in this population would not be able to self-report. The tool has been translated, culturally adapted and validated for children with developmental disorders in Pakistan and indicted satisfactory psychometric properties in terms of internal consistency, construct validity and factor structure (*Hamdani et al. forthcoming*).

### Secondary intervention effectiveness outcomes

*Caregiver–Child Interaction* (Baggett *et al*. 2009): Fifteen minute video taped caregiver–child interactions will be collected at baseline and at endpoint for families in both arms of the study. Caregivers will be asked to try home routines involving the child (e.g. feeding the child performing domestic chores) or play based routines (e.g. playing with toys or reading a book) with their child. Caregiver's facilitators and interrupters and child's engagement and distress during social communication and joint engagement will be rated. The CCI videos will be singly coded by trained assessors.*Clinical Global Impressions* (**McConachie *et al*. 2015**): CGI ratings for focusing on the child's social communication challenges will be conducted at baseline and endpoint. The CGI ratings include two scores: (a) severity of challenges in social communication (rated from 1–7) and (b) improvement in social communication from entry to exit (rated from 1–7).*Socio emotional well-being of children* (Goodman, **1997**): Strength and Difficulties Questionnaire (SDQ) is a Parent rated, 25 items scale distributed over five domains: emotional symptoms; conduct problems; hyperactivity/inattention; peer relationship problems, and; prosocial behavior. Each item is rated on a 3-point Likert scale (0 = not true, 1 = somewhat true, 2 = certainly true). Total difficulty score is calculated by adding the scores of all domain except prosocial behavior items (Goodman, 1997). SDQ has been validated in Pakistani and has shown good psychometric properties (Samad *et al*. 2005; Syed *et al*. 2007).*Parental health related quality of life* (**Varni *et al*. 1999**): Parental health related quality of life will be measured by Pediatric Quality of Life (Peds-QL) Family impact module. The Peds-QL is 36 item impact module scale that encompasses 6 sub-scales measuring parent self-reported functioning. These subscales measure physical functioning, emotional functioning, social functioning, daily activities and family relationships. Items are rated on a 5 point Likert scale (0 = never to 4 = almost always). Peds-Ql has shown sound psychometric properties in different cultures (Scarpelli *et al*. 2008; Chen *et al*. 2011).*Family empowerment measured by Family Empowerment Scale (FES)* (**Koren *et al*. 1992**): The family empowerment scale (Koren *et al*. 1992) is a parent rated, 34 items scale consisting of three subscales. The family subscale (12 items) refers to the parents’ management of everyday situations. The service system subscale (12 items) refers to parents’ acting to obtain services to meet the child's needs. The community subscale (10 items) refers to parents’ advocacy for improving services for children in general. Each item is rated on a 5-point Likert scale (1 = not true at all to 5 = very true). Scores are summed across all items for each subscale with higher scores indicating relatively more empowerment. FES has shown good internal consistency, test-retest reliability and factor structure (Koren *et al*. 1992).*Caregivers’ stigmatizing experiences measured by Inventory of Stigmatising Experiences (ISE)* (Stuart *et al*. 2005): This is an interview based measure of the extent of stigma faced by family. Consisting of Seven items, each item is rated on a 5-point liker scale (1 = never to 5 = always). The responses are recoded into a binary variable with 1 reflecting presence of stigma and 0 reflecting absence of stigma. Scores are summed across all items with a maximum score of 7, with lower scores indicating relatively less stigma. The scale indicated good internal consistency (Stuart *et al*. 2005).*Life Events and Social Factors*: A translated and culturally adapted version of Life Events and Disability Schedule (LEDS) (Husain *et al*. 2000) will be administered at follow up to measure the exposure to any potential negative life event/s that happened since the baseline assessment.

### Implementation effectiveness outcomes

*Applied Mental Health Research Dissemination and Implementation measurements (AMHRG, Personal communication)*: The effectiveness of implementation will be measured by an adapted version of AMHR D& I measurement tool. The consumer, provider and organizational versions of instrument will be administered at 6 months follow up. The consumer instrument consists of scales to measure Acceptability (17 items), Adoption (12 items), Appropriateness (13 items), Feasibility (14 items), and Penetration (8 items).

The provider level instrument contains 16 items to measure Acceptability, 9 items for Adoption, 16 items for Appropriateness, 20 items for Feasibility, 8 items for Penetration and additional scales to measure Organisational Climate (13 items), and Organisational Leadership (10 items).

At the organisational staff level there are 10 Acceptability items, 13 Adoption items, 12 Appropriateness items, 14 Feasibility items, 8 Penetration items, 15 Organisational Climate items and 10 Organisational Leadership items. Each item is scored on a 4-point ordinal scale ranging from 0 ‘not at all’ to 3 ‘a lot,’ with an additional category for ‘don't know/not applicable.’

The tool was tested using mixed methods as part of a project focused on scale-up of evidence-based mental health programs in Iraqi Kurdistan and Myanmar. Reliability results showed adequate internal consistency reliabilities (ranged from 0.61 to 0.95).
*Cost*: The cost of implementing the WHO PST Program delivered by Family volunteers at scale will be calculated using the project financial data. Service utilization and out of pocket expenditure of the study participants (costs for: seeing a doctor or other health care providers; admission to hospital, medicines, tests and extra help at home needed, the utilization of various health and social care services including time and opportunity losses by the families in the care of their child with developmental delay/disorder) will be collected in the trial at baseline and 6 months follow up. Health services utilisation by the trial participants will be measured using the Client Service Receipt Inventory (Chisholm *et al*. 2000) that has been adapted for use in children and families with developmental disorders and delays.

### Masking

Given the nature of WHO PST programme intervention, it is not possible to mask the participants and facilitators, as well as the qualitative research team staffs. All researchers conducting pre-post quantitative outcome assessments will be masked in the trial. The order of outcome measures ensures that the primary outcome measure (WHODAS) is administered first as this will minimise the risk of bias that can happen if masking is compromised. If unmasking does occur this will be documented, the assessment halted, and a new researcher assigned to complete assessments with that participant.

The trial statistician will also be blinded regarding the treatment code when he develops the statistical analysis plan and writes the statistical programmes, which will be validated and completed using dummy randomisation codes. The actual allocation will only be provided to the study team after lock of the database.

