### Procedure to identify eligible participants

Prior to randomisation, key stakeholders (village elders and the primary health care staff) will be informed about the study procedures and their permission will be sought. HDRF has a database of about 3000 families and children with developmental disorders and delays gathered by interactive voice response (Hamdani *et al*. 2015) and snowballing sample technique as a part of the Foundation's service delivery to the community.

For the purpose of the trial we will need to identify 540 parent-child dyads from within 30 clusters (18 parent-child dyads from each cluster) to complete baseline and endpoint assessments. However according to the existing database of children, we expect that in each UC/cluster there will be more than 18 children fulfilling the eligibility criteria. For the purpose of the trial, within each UC, evaluation zones will be made to assess the impact of PST programme for children with developmental disorders and delays delivered by family volunteers.

These evaluation zones will be made by randomly selecting one LHW out of the total 15–20 LHWs serving a particular UC. The random selection will be carried out by an independent researcher not involved in the trial using a simple random table. If the required number of dyads is not completed from one LHW catchment area, we will include the catchment areas of adjacent LHW to reach the required sample size from each UC. This patch of contiguous area/catchment areas of LHWs within that UC will serve as the impact evaluation zone for our trial related outcomes.

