### Randomisation

As it is a cRCT, unit of randomisation is cluster. Each cluster is the smallest administrative unit, called UC. Thirty UC clusters will be randomised to the intervention and control arms on a 1:1 allocation ratio using a permuted-block randomisation method. SAS PROC PLAN is carried out to generate a randomisation list by an independent statistician based at University of Liverpool. Allocation of clusters will be carried out by an independent person not involved in the conduct of the trial.

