### Informed consent

The trained research team along with LHW will approach the families within the evaluation zones of the UCs to seek informed consent for participation in the trial. For the families who consent for participation in the trial, the research team will evaluate caregiver-child dyad against trial inclusion and exclusion criteria. Baseline assessments will be completed for consenting parent-child dyads. LHW will inform the families about the allocation status. Families randomised to intervention arm will be organised into networks with one champion family volunteer for 5–7 families. A record of outcome of screening, assessment against eligibility criteria, and reasons for refusal will be maintained for those who do not consent for participation in the trial. At the endpoint, researcher will verbally reaffirm the consent.

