### Outcomes evaluation

Baseline and end point assessments (6 months post intervention) on the sample of 540 parent-child dyads will be conducted by the trained research assessment team blind to the allocation status of the trial participants. Research assessment team is trained in administration of all outcome assessment tools, interviewing techniques, and principles of good clinical practices. The assessments will be completed at a venue of participant's choice-either at their own house, or the LHWs house called the ‘Health House’ or at any other household within the community.

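### The unmasking rule replaces the assessor for one participant only, although allocation is by Union Council and one disclosure reveals the arm of every other dyad there

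*Protocol article*

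**What the plan says.** The Masking section commits the trial to masked assessors for all quantitative outcomes and accepts that participants and facilitators cannot be masked. It gives two safeguards. WHODAS is administered first within each assessment. If masking fails: "If unmasking does occur this will be documented, the assessment halted, and a new researcher assigned to complete assessments with that participant".

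The Randomisation section fixes the unit of allocation: "As it is a cRCT, unit of randomisation is cluster. Each cluster is the smallest administrative unit, called UC". It continues: "Thirty UC clusters will be randomised to the intervention and control arms on a 1:1 allocation ratio". The section on identifying eligible participants plans 18 dyads per UC, taken from one contiguous evaluation zone.

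Under Informed consent, after the baseline assessments, "LHW will inform the families about the allocation status". Under Outcomes evaluation, assessments take place within the community, at a venue the participant chooses. The primary outcome is the interviewer-administered caregiver-report version of WHODAS-Child.

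**The concern.** Replacing the assessor for the affected participant is enough when participants are randomised individually, because one person's allocation then says little about the next person's. Here all dyads in a UC are in the same arm. A remark by one caregiver tells the assessor the arm of the whole UC, and the assessor knows which UC the next family lives in.

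The stated rule deals with the interrupted interview and stops there. No other section of the article takes the unmasked assessor off the remaining dyads in that UC.

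What is at stake is protection against detection bias on an interviewer-administered primary outcome. Any influence of a known allocation would run in the same direction for all later dyads that assessor sees in the UC. It would be tied to arm, so the random cluster effect in the primary model would not remove it. The problem lies mainly at endpoint, since families learn their allocation after baseline.

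**Working it through.** **The plan's own figure.** The only related number in the article is the 93% power.
- Dyads after 15% attrition: 540 × 0.85 = 459, or 15.3 per UC.
- Design effect: 1 + (15.3 − 1) × 0.01 = 1.143.
- Effective number per arm: 229.5 / 1.143 = 200.8.
- Power for an effect of 0.35 SD, two-sided 5%: 93.9% by the normal approximation, 92.3% with a t-test on 28 degrees of freedom.

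The stated figure reproduces, and this point does not change it.

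**Scope of the rule against scope of the knowledge.**
- Covered by the rule: one dyad ("a new researcher assigned to complete assessments with that participant").
- Revealed by one disclosure: the arm of all 18 dyads, so 18 − 1 = 17 others, or about 14 after attrition.
- Covered by giving WHODAS first: at most the disclosing dyad, and only if disclosure comes after WHODAS is finished. For a later dyad in the UC the arm is known before the first item.

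**How many later dyads one assessor might still see.** The number of assessors per UC is not stated. If 18 dyads are shared equally:

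| Assessors per UC (assumed) | Dyads each | Most that can follow a disclosure | Average, if disclosure falls at a random point |
|---|---|---|---|
| 1 | 18 | 17 | 8.5 |
| 2 | 9 | 8 | 4 |
| 3 | 6 | 5 | 2.5 |

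**Share of endpoint dyads assessed after a disclosure.** Assumptions: 15 endpoint dyads per UC (18 × 0.85 = 15.3, rounded); an independent chance p of disclosure at each interview; assessors who do not share what they learn; and an unmasked assessor who carries on in the UC. With k dyads per assessor, the dyad in position j follows a disclosure with probability 1 − (1 − p)^(j−1). Averaging over j = 1 to k gives

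share = 1 − [1 − (1 − p)^k] / (k p).

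Worked example, k = 15 and p = 0.05: 0.95^15 = 0.463; (1 − 0.463) / 0.75 = 0.716; share = 0.284.

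| p (assumed) | UCs with at least one disclosure, 1 − (1 − p)^15 | Share, one assessor (k = 15) | Share, three assessors (k = 5 each) |
|---|---|---|---|
| 2% | 26% | 13% | 4% |
| 5% | 54% | 28% | 10% |
| 10% | 79% | 47% | 18% |

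These are shares of assessments exposed to a known allocation. Turning them into bias would need the effect of assessor knowledge on WHODAS-Child scores, which the article does not give.

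**The case against.** The strongest reply is that silence is not permission. The Masking section sets a general requirement that all outcome assessors be masked, and an assessor who carried on knowing the arm would breach it. The sentence on unmasking may only describe what to do with the interrupted interview, with redeployment left to a field manual. This stands in part. A reader might infer that the plan orders the unmasked assessor to continue; it does not, it leaves the matter open. But the article does state a remedy and limits it to the participant concerned, so field staff following it to the letter would have no instruction for the other dyads.

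A second reply is that the exposure figures rest on assumed inputs, and that one assessor per UC is the worst case. That is correct, and is why the three-assessor range belongs beside it.

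Third, caregivers report the primary outcome and know their arm in every dyad, so the extra effect of an unmasked assessor is unknown. This stands. A reader might infer that masked assessment fails altogether, and the article does not support that.

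Fourth, one might infer from the listed venues ("at their own house, or the LHWs house called the" Health House) that disclosure is more likely there, because the lady health worker tells families their allocation. The article does not say that she attends the interview, and the venue is the participant's choice. That inference is conjecture, and restricting venues has its own cost.

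**Conclusion.** The point holds as a mismatch between a stated safeguard and the trial's own allocation scheme. The rule protects one dyad, while the disclosure reveals the arm of up to 17 others in the UC. Neither the rule nor the order of the instruments protects the dyads that the same assessor sees afterwards. This follows from the text and needs no assumption.

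The practical size is uncertain. Under the assumptions shown, between about 4% (three assessors, 2% risk) and 47% (one assessor, 10% risk) of endpoint dyads would be assessed after a disclosure. The number of assessors and the disclosure risk are both assumed, and the range presumes that unmasked assessors continue in the UC. Neither the size of any bias in the treatment effect nor an effect on the study's conclusion can be derived from the article. The sample size and the primary model are not in question.

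**What to change.** Extend the rule in the Masking section: an assessor unmasked for any dyad does no further outcome assessments in that UC, and the remaining dyads there pass to another member of the existing team who is still masked. Log every unmasking by UC and date, and report it by UC, arm and date. The arm can be attached after database lock, so that the log does not itself unmask anyone.

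The cost is one amended sentence, some re-rostering and some travel. The present rule already presumes that a replacement researcher can be found, although team size is not stated. The Trial status section says that recruitment had begun and the trial was ongoing, so the change can protect only assessments still to be made; for earlier ones, reporting what happened is the remedy.

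No restriction on venue is needed. An analysis that leaves out dyads assessed by an unmasked assessor should be labelled exploratory. It conditions on an event after randomisation, and if families in one arm disclose more often, the exclusions would differ by arm.

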### Data management

*Quantitative data*: The pre-post data from study participants will be collected by the assessment team using hand held devices (Tablets) with pre-assigned participant codes. Database will be stored in password protected computers and backed-up on daily basis. The data will be downloaded into SAS and SPSS formats for statistical analysis.

*Qualitative data*: Anonymised data will be stored in paper format in locked filing cabinets in the field office.

### Statistical methods

Findings of the trial will be reported following the recommendations of the CONSORT 2010 statement: extension to cluster randomised trials (Schulz *et al*. 2010) (See Fig. 3).

**Fig. 3. fig03:**
[figure not shown]
CONSORT flow chart.

All the analysis will be based on intention to treat. Data will be analysed using SAS 9.3 and SPSS Version 21. To estimate the treatment effect, a linear mixed model will be employed for the primary endpoint analysis, which will have treatment as fixed effect, and baseline measurement of primary endpoint as covariate, and cluster as random effect. The mean difference between two treatment arms at 6 months together with its 95% confidence interval will be derived from the mixed model. Covariate-adjusted mixed model of primary endpoint will also be performed by adding pre-specified covariates at baseline into the above model. Subgroup analysis will also be performed for the pre-specified covariates used in the covariate adjusted analysis.

### Qualitative and quantitative methods to answer research questions 3 and 4

The updated implementation research framework by Proctor *et al*. (2011) have identified eight key constructs of implementation research. We will collect data on the implementation outcomes at 6 months post program implementation using an adapted version of AMHR D&I measurement tool. Other implementation indicators that will be collected during the program delivery include
Number and duration of sessions delivered: Information will be collated from the log books of the conducted sessions, which will record basic information about the session – the date, time, and duration of the session.Number of participants who completed the treatment and have a planned discharge.Number of Family Networks established by family volunteers within their allocated vicinity.

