### Participants’ recruitment

#### Inclusion criteria

Children aged between 2 and 12 years residing in the study area for the duration of the study will be invited to participate in the trial. Inclusion criteria are as follows:
Children who are screen positive on any of the Ten Questions Screen questionnaire items # 1,4,5,7,8,9,10 for neurodevelopmental delay (Durkin *et al*. 1995)Diagnosed as developmental disorder/delays according to clinical assessment (History & clinical examination for developmental delay in motor, communication, social, cognitive, daily living skills domains according to mhGAP developmental disorders guidelines for clinical assessment in primary healthcare settings.

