### Sample and power calculations

The effect size estimates for the primary outcome measure (WHODAS-Child) are informed by the results of the pre-post feasibility study in Pakistan (Hamdani *et al*. 2015) and are in line with the effect sizes reported in a recent WHO supported systematic review of literature for non-specialist delivered psychosocial interventions for developmental disorders in lower middle income countries (Reichow *et al*. 2013).

We aim for a conservative effect size estimate of 0.35 for the primary and secondary outcome measures in the definitive cluster randomised trial.

We propose to recruit a sample of 540 parent-child dyads in 30 clusters (on average 18 parent-child dyad per cluster), equally distributed among the intervention and control arms. This will give 93% power at 5% two sided significance level with an ICC of 0.01 and will account for 15% attrition rate.

Since the study addresses developmental disorders and delays, which are manifested in multiple ways, we expect the clusters to be heterogeneous with respect to diagnosis, severity, age and co-morbid conditions, hence we have chosen a lower value of ICC of 0.01.

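### The primary model leaves out the child's age although one WHODAS-Child score covers ages 2 to 12; adding it would give a modest gain in precision if age predicts the endpoint beyond baseline

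*Protocol article*

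**What the plan says.** In the protocol article, Statistical methods (the text after Fig. 3), the primary endpoint is analysed by a linear mixed model "which will have treatment as fixed effect, and baseline measurement of primary endpoint as covariate, and cluster as random effect". The 6-month mean difference and its 95% confidence interval come from this model. The section then adds a second analysis: "Covariate-adjusted mixed model of primary endpoint will also be performed by adding pre-specified covariates at baseline into the above model". Subgroup analyses use the same covariates, which the article does not name.

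On age, the Inclusion criteria state: "Children aged between 2 and 12 years residing in the study area for the duration of the study will be invited to participate". On the instrument, the primary outcome section states: "The WHODAS is a 36-item questionnaire measuring functioning and disability". It is completed by caregiver report and covers cognition, mobility, self-care, getting along with others, life activities and participation. No age bands or age norms are described.

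Under Sample and power calculations the authors write "we expect the clusters to be heterogeneous with respect to diagnosis, severity, age and co-morbid conditions", as their reason for a low ICC. The same section states "We aim for a conservative effect size estimate of 0.35 for the primary and secondary outcome measures" and "This will give 93% power at 5% two sided significance level with an ICC of 0.01 and will account for 15% attrition rate". Under Randomisation, 30 Union Councils (UCs) are allocated 1:1 by permuted blocks, and no stratification factor is mentioned.

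**The concern.** A functioning score that includes self-care, mobility and life activities may depend on age. The endpoint falls six months after a programme of nine weekly sessions, so children of different ages who start with the same score may change by different amounts. Baseline WHODAS may not fully carry that difference. If it does not, age-related variation stays in the residual and the primary interval is somewhat wider than it need be.

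With 15 clusters per arm, mean age can also differ between arms by chance. The single realised estimate would then carry part of that difference. Age is recorded for every dyad, but under the stated plan it can enter only the additional adjusted model, not the one that yields the primary estimate.

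**Working it through.** **The plan's own figure first.** Inputs from Sample and power calculations: 540 dyads, 30 clusters, effect 0.35 SD, ICC 0.01, 15% attrition, two-sided 5%.

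- Analysed: 540 × 0.85 = 459, so 459/30 = 15.3 per cluster.
- Design effect: 1 + (15.3 − 1) × 0.01 = 1.143.
- SE of the difference in SD units, with no covariate credited: √(4 × 1.143/459) = 0.0998.
- Power, normal approximation: Φ(0.35/0.0998 − 1.96) = Φ(1.55) = 93.9%. Keeping the design effect at 18 per cluster (1.17) gives 93.4%; a t reference with 28 df gives 92.3%.

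The stated 93% is reproduced, and it does not depend on age.

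**Precision gained by adding age.** Let p be the partial correlation of age with the 6-month score given baseline WHODAS. The article gives no value, so p is assumed. The interval width is multiplied by √(1 − p²), and the equivalent number of extra completers is 459/(1 − p²) − 459.

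| p (assumed) | Interval narrower by | Extra completers |
|---|---|---|
| 0.1 | 0.5% | 5 |
| 0.2 | 2.0% | 19 |
| 0.3 | 4.6% | 45 |

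**Is that range of p plausible once baseline is in the model?** Suppose age correlates a with both the baseline and the 6-month score, and the two scores correlate r. Then p = a(1 − r)/√((1 − a²)(1 − r²)). Over assumed ranges a = 0.2 to 0.6 and r = 0.5 to 0.8, p runs from 0.07 to 0.43 and the narrowing from 0.2% to 9.9%. For a = 0.3 it is 0.6% to 1.7%; for a = 0.5 it is 1.9% to 5.7%. Gains above 5% need a strong age correlation, and the largest also need a weaker baseline correlation. If p is 0, there is no gain.

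**Chance age imbalance.** Assume age is uniform over 2 to 12, so its SD is 10/√12 = 2.89 years, with an age ICC of 0.01 to 0.05.

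- ICC 0.01: design effect 1.143; SE of the mean-age difference 2.89 × √(4 × 1.143/459) = 0.29 years.
- ICC 0.05: design effect 1 + 14.3 × 0.05 = 1.715; SE 2.89 × √(4 × 1.715/459) = 0.35 years.
- 95% limits (1.96 × SE): about ±0.6 to ±0.7 years, or 0.20 to 0.24 SD of age.

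**Effect on the estimate.** If baseline WHODAS differs between arms as the age difference d (in SD) would predict, the shift left after baseline adjustment is a(1 − r)d.

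- a = 0.3, r = 0.7, d = 0.20: 0.09 × 0.20 = 0.02 SD.
- a = 0.5, r = 0.5, d = 0.24: 0.25 × 0.24 = 0.06 SD.

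If baseline WHODAS happened to be balanced despite the age difference, the factor becomes a(1 − r)/(1 − a²). The second case is then 0.333 × 0.24 = 0.08 SD. For scale, the target is 0.35 SD. The 95% half-width without age is 1.96 × 0.0998 × √(1 − r²): 0.17 SD at r = 0.5 and 0.14 SD at r = 0.7.

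**The case against.** The strongest reply is that the stated model is sound. It respects the clustering and adjusts for the baseline outcome, and baseline WHODAS will already carry much of any age effect on the level of the score. A covariate-adjusted model is planned too, and age may be on its list; an article may leave that list to the analysis plan, so its absence here is no fault. Power does not depend on age. Chance imbalance under randomisation is not bias, and the interval already allows for it. Changing a published primary model after recruitment began in March 2016 is also a formal amendment.

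All of this stands, and it limits the point to an optional improvement. It does not remove it. Even if age is on the unnamed list, the article places that list outside the model that gives the primary estimate.

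Three stronger readings are tempting and not supported:

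- A reader might infer that the primary interval is certainly too wide, or that baseline WHODAS fails to carry age-dependent change. The article gives no correlation of age with WHODAS, and its silence on age norms does not show that there are none.
- A reader might take the expected age heterogeneity as evidence that age is prognostic. That sentence describes the clusters and justifies the ICC. Clusters that are each mixed in age would, if anything, make a between-arm age difference less likely.
- A reader might infer that selective recruitment adds to the imbalance. The article has an independent researcher select the Lady Health Worker areas at random, and it places informing families of allocation after baseline assessment. It gives no figure for such selection.

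**Conclusion.** The point holds as a modest, conditional gain in precision. Age is absent from the primary model, one score spans ages 2 to 12, and the covariate is already available. The primary 95% interval would narrow by about 0.5%, 2.0% or 4.6% at assumed partial correlations of 0.1, 0.2 or 0.3. The shift from chance age imbalance at its 95% limit is about 0.02 to 0.06 SD. That second figure assumes uniform age, an age ICC of 0.01 to 0.05, age correlations of 0.3 to 0.5, baseline correlations of 0.5 to 0.7, and a baseline score that moves with age.

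None of this shows bias in the randomised comparison, a shortfall in power or a contradiction in the plan.

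**What to change.** Before database lock, while the statistician is still masked (see Masking), define the primary model as treatment, baseline WHODAS-Child and baseline age (continuous) as fixed effects, with UC as random effect. Report the model now stated as a sensitivity analysis. The planned covariate-adjusted model and subgroup analyses can stay as they are.

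The cost is one degree of freedom and a documented, dated amendment to the primary analysis. No new data are needed.
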